## Abstract

**Background:**

Postoperative delirium and cognitive deficits are significant surgical complications, especially in elderly patients. The reported incidence of postoperative delirium is variable but notably high in cardiothoracic, orthopedic, and general surgery. The etiology of postoperative delirium is known to be multifactorial, with prevention being the most effective strategy currently available. This study aims to explore the potential benefits of positive suggestions delivered via headphones during general anesthesia on the incidence of postoperative delirium and improving postoperative pain, nausea, and cognitive outcomes in elderly orthopedic patients.

**Methods:**

This randomized controlled double-blinded trial will involve patients aged 60 and above undergoing elective hip or knee surgery under general anesthesia. Participants will be randomized into three groups: a control group receiving no auditory intervention and two intervention groups receiving positive therapeutic suggestions via headphones from either a male or female speaker. The primary outcome is the incidence of postoperative delirium within 5 days after surgery that will be assessed by using the 4AT and 3DCAM. Secondary outcomes include pain intensity, which is measured intraoperative by nociception level index (NOL) and postoperative by NRS, medication consumption as well as postoperative nausea and vomiting. Data will be collected before, during, and after surgery as well as 3 months after surgery.

**Discussion:**

This study hypothesizes that positive auditory suggestions can reduce postoperative delirium incidence, lower pain intensity as well as pain medication use, and decrease postoperative nausea, vomiting incidence, and severity. Additionally, gender differences in response to male versus female voices will be explored. The findings could offer a non-invasive, cost-effective method to enhance postoperative recovery in elderly patients, potentially leading to changes in perioperative care practices.

**Trial registration:**

DRKS00030589 prospectively registered 25.10.2022.

## Introduction

### Background and rationale {6a}

#### Postoperative syndromes with cognitive deficits

Postoperative delirium (POD) is an acute neuropsychiatric syndrome. It is characterized by transient disturbances in attention, awareness, and cognition following surgery [1]. It typically manifests within the first few days after an operation and is marked by fluctuating symptoms, including confusion, disorientation, an altered level of consciousness, and impaired memory. POD is more common in elderly patients and those having major surgery. The incidence of POD varies widely and depends on the age of the patient cohort studied and the type of surgical procedure [2]. The highest incidences are found after cardiothoracic procedures, orthopedic and general surgery [3]. While the exact etiology is best described as multifactorial and not fully understood to date [4], it is known to be associated with increased morbidity, prolonged hospital stay, an elevated risk of long-term cognitive decline as well as increased mortality [5]. For example, Moskowitz et al. demonstrated that for elective surgery, in patients 50 or more years of age, 5-year mortality was increased 7.35-fold after the occurrence of POD (95% CI, 1.49–36.18) [6].

Postoperative cognitive dysfunction (POCD) describes a measurable decline in cognitive domains such as memory, attention, and processing speed that occurs after surgery, particularly in older adults [7]. According to the recommendations of the Nomenclature Consensus Working Group [8], POCD refers to cognitive decline identified at least 30 days after surgery and persisting for up to 12 months postoperatively, with cognitive changes detected within the first 30 days classified as delayed neurocognitive recovery. Although POCD is often transient, resolving within weeks to months, it may persist in some cases for extended periods. Potential contributing factors include the effects of anesthesia, surgical stress, and perioperative complications [39].

Neurocognitive disorder (NCD), in contrast, refers to a more sustained decline in cognitive abilities that is severe enough to interfere with everyday functioning.

As the development of POD or long-term POCD represents the most frequent postoperative complication, mainly affecting elderly patients [9], a further increase of this complication is expected in the future due to demographic change [6]. As prevention has proven most effectively [3], patient’s personal risk factors and possible predictors must be identified and measures to reduce the probability of the occurrence of POD/POCD or NCD [10] must be taken.

#### Importance of therapeutic communication

Communication plays a special role in the entire field of healthcare. It can accompany and support medical therapies. Appropriate use of language and professional conversation management allow us to discover patients’ resources and use them for the process of healing.

A randomized, double-blind, multicenter trial showed that audio cues can reduce pain and nausea, consequently reducing the use of analgesics and antiemetics in at-risk groups. The time to reorientation was also shown to be diminished [11]. Due to the age structure of the study, delirium incidence was inherently low, so no conclusions could be drawn regarding the antidelirogenic effect of positive suggestions.

#### Objectified intraoperative pain measurement

Measuring pain intensity is usually based on self-reporting by patients. With this method the subjective level of pain can be determined before and after surgery. Since patients cannot be questioned during general anesthesia, it was not possible to measure pain level intraoperatively in the past. Lately, an AI-based algorithm has been developed to generate a Nociception Level Index (NOL) during surgery [12]. The algorithm considers variants of the following four parameters, which can be measured via a single finger electrode: Skin conductance, heart rate variability, accelerometry, and skin temperature. Studies have already shown that the NOL index is suitable for predicting postoperative pain [13]. Thus, this technology seems to be suitable for a more precise analysis of the effect of therapeutic interventions especially on perioperative pain perception.

#### Gender differences: effect of different voices

Gender acts as an independent risk factor for several diseases and disorders. For example, female gender has already been established as a specific risk factor for the occurrence of postoperative nausea and vomiting [14]. The opposite seems to be true for the occurrence of delirium after surgical interventions: In this context, men seem to be more likely to develop POD [15]. With the upcoming awareness for gender sensitive medicine, research has also increasingly focused on the impact of sex differences on the efficacy of therapeutic interventions. For instance, there appear to be discrepancies in the efficacy of hypnosis therapy for smoking cessation when administered to different sexes (Green et al., 2008). However, robust data on gender differences in the effects of suggestive procedures is missing. In particular, no research has been done on gender differences in the effects of hypnotic suggestion when delivered by different voices.

#### Biomarkers to predict cognitive outcome after surgery

NCD, particularly POD and POCD represent significant complications following surgical procedures. Given that current therapeutic approaches primarily focus on general factors such as, e.g., fluid and electrolyte balance [16], there is a growing emphasis on early diagnosis and prevention of NCD [5]. The identification of high-risk patients in advance is of the utmost importance. For this purpose, biomarkers have been investigated [17]; however, their suitability for routine use is limited due to the invasive nature of the puncture. An alternative approach is to utilize markers in the blood, which can be categorized into three groups: global non-specific markers, established specific markers of neurocognitive functions and markers with less evidence to date. While so far, no single marker on its own has been sufficient for accurate prediction, a targeted combination of different markers could be an effective method for predicting cognitive complications with sufficient sensitivity and specificity [18]. As part of the ethically approved study protocol, perioperative blood samples were collected for the assessment of exploratory biomarkers potentially associated with postoperative cognitive and functional outcomes, such as cortisol, cortisol derivatives, NT-proCNP, NfL, S-100, pTau, and IL-6. These samples will be analyzed in a separate, hypothesis-generating investigation and are not part of the analyses reported in the present manuscript.

This trial will examine whether suggestions can reduce the probability of occurrence of delirium. Furthermore, it will be examined to what extent intraoperative application of different suggestive statements can reduce the postoperative perceived nausea as well as vomiting and pain, measured by the consumption of analgesics at a defined pain level. Moreover, it will be tested whether patients return to spontaneous breathing more rapidly, regain consciousness faster, are oriented and have less anxiety by listening to a sound recording with suggestions compared to a control group.

Potential risk markers for stress, delirium, and inflammation are to be investigated by measuring several parameters in the patients’ blood.

Beside the above mentioned targets, it will be investigated whether the choice of voice (male vs. female) has an influence on the effects described above.

### Objectives {7}

In the current study, we aim to address the following hypotheses:

Primary hypothesis:Delirium incidence is lower in the intervention group than in the control group

Secondary hypotheses:2)Pain intensity is lower in the intervention group than in the control group3)Intraoperative: NOL values are lower in the intervention group than in the control group4)Postoperative: NRS values are lower in the intervention group than in the control.5)Pain medication consumption p.p. is lower in the intervention group than in the control group6)Postoperative nausea and vomiting (PONV) incidence is lower in the intervention group than in the control group

Exploratory analyzation:7)The above-mentioned effects differ depending on whether the subjects hear a speaker’s voice according to their own gender or not

### Trial design {8}

A parallel group design will be applied. The study physician, who is not directly involved in data collection, will randomly assign patients to experimental conditions using software. Every person directly involved will be blinded to the allocation, as will the patients. Included patients will be randomized into 3 groups. In the sense of a balanced design, equal numbers of patients will be assigned to the intervention or control group. The experimental group will be further subdivided. During general anesthesia, patients in both intervention groups will be presented with positive therapeutic content via headphones either from a female or male speaker. Patients in the control group also will receive headphones for general anesthesia, but the track that will be played does not contain any audio content. Otherwise, the treatment will not differ from the verum group. A flow chart of the process of recruiting, including and randomizing patient is shown in Fig. 1.

**Fig. 1 Fig1:**
[figure not shown]
Flow chart

## Methods: participants, interventions and outcomes

### Study setting {9}

All data will be collected in Germany. Leading center of the trial is the hospital of the Munich Ludwig-Maximilians-University (LMU). Further data is planned to be collected in the hospital of the Ruhr University Bochum as well as in the Heidelberg university hospital.

### Eligibility criteria {10}

Patients meeting following criteria will be included:Elective hip or knee surgery (e.g., hip or knee TEP) with a planned duration of 1–3 hGeneral anesthesia using total intravenous anesthesia (TIVA)*Age from 60 years and aboveGerman as native language or similar levelSufficient hearing ability (no hearing aid at room volume necessary)Ability to give consent

The following exclusion criteria apply:Patients with hearing lossDiagnosis of dementia or MOCA < 17Preoperative delirium on hospital admissionLanguage barriersPatient refusalIf consent for blood collection: hemoglobin < 10 g/dL

### Who will take informed consent? {26a}

Prior to surgery, patients who will undergo knee or hip surgery will be seen by a member of the study team who will ask them for their informed consent. If consent will be given, a short assessment will be conducted to evaluate inclusion and exclusion criteria.

### Additional consent provisions for collection and use of participant data and biological specimens {26b}

N/a (patient data will be specifically used for this study).

## Interventions

### Explanation for the choice of comparators {6b}

Delirium is a complication that primarily affects patients of older age. Therefore, patients will be recruited who already reached the age of 60 for all three subgroups. The control group will also receive headphones but without the suggestion audio.

#### Intervention description {11a}

Patients will be randomized with permuted block randomization that stratifies for their gender into a control and a intervention group within a 1:1 ratio. Intervention group will be further randomized 1:1 into a group that listens to audio content spoken by a voice that matches their gender and into a group that listens to a gender incongruent voice. The audio intervention is standardized and developed according to principles of therapeutic suggestion. We used the original text from Nowak et al. [11] as a blueprint for our intervention but adjusted it slightly to match our intentions. With the help of a soundcheck track volume will be set to a comfortable but clearly audible level before induction, with adjustments if necessary, prior to loss of consciousness. The audio content is structured into two segments. The initial segment begins after the intubation of the patient is being completed and therefore after loss of consciousness. It runs continuously (repeatedly) until approximately 15 min before the initiation of the extubation stage. The following text extracts are drawn from the first audio track (translated from the original German suggestion):

Positive suggestions to prevent delirium

*You are now sleeping soundly and deeply and can relax and rest, recover and recharge your batteries, because you are safe and well protected. Everything you hear, see, and feel contributes to your well-being. This allows your body to focus entirely on its self-healing powers. And we are by your side. You hear my voice, it accompanies you, you can concentrate fully on it, because what I tell you is important for you, important for your well-being and your healing.*

Positive suggestions to prevent pain:

*You will feel carefree and unaffected in the hours and days following the operation. You will feel calm, warm, relaxed, and content. Everything you feel will be good for your well-being. It will show you that your body is working hard to repair itself, restore balance, and return everything to normal. Your recovery can progress, unstoppable. Further and further.*

Positive suggestions to prevent PONV:

*Gradually, all your bodily functions will start up again: your circulation will get going, as will your digestion. Saliva will be produced and you will be able to swallow it. And you will be able to drink. Everything will start up again and move in the right direction, namely from top to bottom, from your mouth to your stomach and further and further into your intestines, moving steadily straight ahead. A sense of well-being can spread more and more and you can ask yourself what you feel like eating first. You will then be able to send blood flow back down to the intestines, which have been resting until then. And with all the energy and oxygen, they start working again. You can swallow liquid again And it flows down the esophagus into the stomach And from the stomach it is transported further into the intestines and in the intestines further and further, evenly and unstoppably in one direction: further*

Approximately 15 min before the initiation of the extubation stage, the audio track is being changed: Patients in the intervention group are now exposed to content that is specifically related to the process of waking up and the initial postoperative period. The following (translated from German) text extracts are drawn from the second audio track:

Positive suggestions for initiating wake up period:

*The operation went well and will be completed shortly. The healing process has already begun. You have been able to rest and regain your strength. Now it is time to come back to the here and now. All the fears that you wanted to protect yourself from are no longer necessary, because you are safe and well cared for.*

Positive suggestions to prevent pain:

*All pain that is actually intended to warn you of something is unnecessary, because you will receive every support.*

Positive suggestions to prevent PONV:

*Any nervousness that causes your stomach and digestion to slow down is unnecessary, because everything is running smoothly and normally. You are safe. Your stomach and intestines are getting back on track. Everything is moving in the right direction. You can swallow freely to clear your throat of saliva. You can look forward to drinking and eating. What will be the first thing you feel like eating?*

Positive suggestions to prevent delirium:

*Now shift your attention back from the inside to the outside. See the light, hear the sounds, you become more and more alert and start moving again. You can orient yourself and find your way around. Everything is fine.*

As soon as the propofol application is being stopped to wake up the patient, headphones will be removed. This is considered the end of our intervention. As the trial is double blinded, patients in the control group are presented with two different audio tracks as well, but these are empty tracks. For patients of all groups, there will be no background music withing the audio tracks.

Apart from the audio exposure, perioperative management will be identical in all groups: Anesthesia will be administered as total intravenous anesthesia (TIVA) using propofol for induction and maintenance, combined with sufentanil for intraoperative analgesia. Neuromuscular blockade will be achieved with rocuronium as needed. Depth of anesthesia will be monitored using bispectral index (BIS) monitoring. Standard multimodal analgesia, perioperative antibiotic prophylaxis, and postoperative nausea and vomiting (PONV) prophylaxis (dexamethasone and ondansetron, unless contraindicated) will be provided according to institutional protocols. No other aspects of anesthesia care will differ between study arms.

### Criteria for discontinuing or modifying allocated interventions {11b}

Consent to participate in the study can be withdrawn at any time, without giving reasons or obtaining any disadvantages for further medical care. In case of withdrawal from the study, personal data already obtained will be destroyed. Patients for whom there will be a short-term change in the anaesthetic procedure, e.g., to anaesthesia with sevoflurane, will be considered separately due to the increased risk of PONV.

### Strategies to improve adherence to interventions {11c}

N/a (as all patients will be monitored by a study team member during their surgery, no specific strategy to improve adherence to protocol is necessary).

### Relevant concomitant care permitted or prohibited during the trial {11d}

Participation in other delirium-related intervention studies.

### Provisions for post-trial care {30}

N/a (no special post-trial care needed).

### Outcomes {12}

Primary outcome will refer to delirium incidence. Cognitive testing in form of the 4AT [19, 20] as well as the 3DCAM [21] will be performed pre- and postoperatively on all study participants to determine whether the incidence of delirium is lower in the intervention group than in the control group.

The 4AT is a brief (< 2 min) screening tool for delirium and cognitive impairment. It includes four domains: alertness, abbreviated mental test–4, attention (months backwards), and acute change or fluctuating course. A score ≥ 4 suggests possible delirium. The 3D-CAM is a structured, validated instrument based on the Confusion Assessment Method (CAM) algorithm, optimized for administration in approximately 3 min. It evaluates acute onset or fluctuating course, inattention, disorganized thinking, and altered level of consciousness. A diagnosis of delirium according to 3D-CAM requires the presence of features 1 and 2, plus either feature 3 or 4 [21, 22]. Both assessments will be conducted by trained members of the study group. Correct assessment will be ensured by random checks as well as supervision through a psychologist.

As secondary outcomes postoperative nausea will be assessed with the Wengritzky PONV score [23], pain will be assessed using the Numerical Rating Scale (NRS) for subjective measurement and using the NOL index for objective measurement. Medication consumption will be documented by analyzing the patient’s files.

Furthermore, the effect of different speaker voices will be investigated as an exploratory analysis.

### Participant timeline {13}

The study duration for all included participants will be defined by the time of surgery until the day of discharge. A follow-up survey of the cognitive function level is planned after 3 months (follow up). The postoperative follow-up point in time was determined by the fact that, at this juncture, patients have customarily concluded their postoperative inpatient rehabilitation and have resided in their domestic environment for a period of several weeks. This period represents the earliest time frame in which daily functioning can be meaningfully assessed, without the confounding influence of ongoing rehabilitation measures or acute postoperative recovery processes. Therefore, it enables a valid evaluation of cognitive performance and its effect on daily living activities under stable conditions. Moreover, the timing of the follow-up assessment is consistent with international recommendations for the evaluation of postoperative POCD and associated outcomes. Evered et al. propose that cognitive testing for POCD should be conducted a minimum of 3 months after surgery, with the aim of avoiding the capture of transient, early postoperative changes [8]. While the MoCA was administered at baseline as an inclusion criterion to confirm adequate cognitive status at 3-month follow-up, no cognitive screening tool was applied. Instead, the assessment focused on functional outcomes using the SF-36 and iADL, as these measures are more directly aligned with capturing everyday functioning. Given the nationwide recruitment, follow-up instruments were selected to allow remote completion and ensure high response rates. Table 1 shows a detailed overview of the course of the study.

**Table 1 Tab1:** Participant timeline

	STUDY PERIOD													
Date	Prior to surgery		Day of surgery						Day 1	Day 2	Day 3	Day 4	Day 5	+3 months
Timepoint	Screening	Baseline	Pre-OP	OP	PostOP recovery room				PostOP ward					Follow-Up
Visit-Code	SCR	V0	V1	V2	V3a	V3b	V3c	V3d	V4	V5	V6	V7	V8	V9
ENROLMENT														
Eligibility criteria	●													
Informed consent	●													
Feedback request	●													
ASSESSMENTS														
MOCA		●												
TMT		●												
Frailty Screening		●												
PONV risk-score		●												
Charlson Comorbidity Index		●												
Permanent medication		●												
QUESTIONNAIRES														
iADL		●												●
SF36		●												●
GDS		●												●
BDI														●
Complications														●
ALLOCATION														
Randomized allocation		●												
SAMPLES														
Blood sample			●											
Saliva sample			●											●
INTERVENTION														
Controll group				●										
SGS intervention group				●										
DGS intervention group				●										
OUTCOME VARIABLES														
4AT Delirium			●		●	●	●	●	●	●	●	●	●	
3DCAM Delirium								●	●	●	●	●	●	
Pain score (NAS)			●		●	●	●	●	●	●	●	●	●	●
Pain medication consumption			●					●	●	●	●	●	●	●
Comfort scale (NCS)			●		●	●	●	●	●	●	●	●	●	●
PONV wengritzky								●	●	●	●	●	●	
Sedline				●										
NOL				●										

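### The 3-month visit is presented as an evaluation of cognition, but no cognitive test is given at that visit

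*Protocol article*

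**What the plan says.** The Background of the abstract includes among the study's aims "improving postoperative pain, nausea, and cognitive outcomes in elderly orthopedic patients". The introduction, under Postoperative syndromes with cognitive deficits, describes POCD as "a measurable decline in cognitive domains such as memory, attention, and processing speed that occurs after surgery" and gives its time window: "POCD refers to cognitive decline identified at least 30 days after surgery and persisting for up to 12 months postoperatively".

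Participant timeline {13} then sets out the 3-month visit. It opens with "A follow-up survey of the cognitive function level is planned after 3 months". It explains why 3 months was chosen and concludes: "Therefore, it enables a valid evaluation of cognitive performance and its effect on daily living activities under stable conditions". It adds that the timing agrees with a published recommendation on when to test for POCD. Later in the same section it says that, at this follow-up, "no cognitive screening tool was applied", and that SF-36 and iADL were used to capture function, chosen so that they could be completed remotely.

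Table 1 and the paragraph After surgery in {18a} match the last statement: V9 is a mailed questionnaire set with pain and comfort ratings and a saliva sample.

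**The concern.** A recommendation on when to carry out cognitive testing cannot justify the timing of a visit that contains none, and a visit without a cognitive measure cannot give a valid evaluation of cognitive performance. The section therefore claims a property that the schedule does not have.

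What is at stake is the scope of the conclusions. If the text stands, the article commits the authors to a 3-month statement on cognition for which there will be no data. The only V9 measures that differ from simple symptom ratings are questionnaires on function, quality of life and mood. A difference between arms on these, or the lack of one, says nothing definite about memory, attention or processing speed.

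**Working it through.** The plan gives no figure on this point, so the check sets the text against the schedule.

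**Step 1: where each instrument is marked in Table 1.**

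| Instrument | Visits marked | At V9 (3 months)? |
|---|---|---|
| MoCA | V0 | no |
| TMT | V0 | no |
| 4AT | V1, V3a to V3d, V4 to V8 | no |
| 3D-CAM | V3d, V4 to V8 | no |
| iADL, SF-36, GDS | V0, V9 | yes |
| BDI | V9 | yes |
| Pain score, comfort scale | V1, V3a to V8, V9 | yes |
| Pain medication | V1, V3d to V8, V9 | yes |
| Saliva sample | V1, V9 | yes |
| Complications | V9 | yes |

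The first four rows are the only instruments in the schedule that test cognition directly. Number given at V9: 0 of 4.

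**Step 2: against the article's own POCD window.** The window opens 30 days after surgery and runs to 12 months. The last 4AT and 3D-CAM are at V8, day 5, so they end 30 − 5 = 25 days before it opens. V9, at 3 months, lies inside the window but has no test. No cognitive test therefore falls in the window.

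**Step 3: change from baseline.** This needs the same test at V0 and at a later visit. MoCA and TMT have one time point each, so patients with a computable change in either number 0 of the planned 280.

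**Step 4: can the V9 questionnaires stand in?** The introduction defines POCD by decline in cognitive domains. {13} itself calls SF-36 and iADL functional measures, and the Baseline paragraph of {18a} describes SF-36 as a quality-of-life questionnaire. The document gives no rule for deriving cognitive status from them. They support a statement about function, not about cognition.

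**Step 5: baselines available for V9 measures.** iADL, SF-36 and GDS each have a V0 value. BDI has none. The covariates named for the regression models in {20a} are medication variables; baseline scores are not mentioned.

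**Side note on anxiety.** The end of the introduction (subsection on biomarkers) says it will be tested whether patients "regain consciousness faster, are oriented and have less anxiety by listening to a sound recording". None of the 14 visit columns has a dedicated anxiety instrument. GDS and BDI are depression scales, the NCS rates comfort, and {33} describes salivary cortisol as a marker of stress.

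**The case against.** The omission is disclosed and explained. {13} says outright that no cognitive tool was used at 3 months and gives remote completion and response rates as reasons. Choosing functional instruments is a legitimate design decision, and POCD appears mainly as background. All of this stands, and it limits how serious the point is. It does not remove the contradiction, because the claim of a valid cognitive evaluation and the POCD timing argument remain in the same section.

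A reader might infer more than the document supports in three ways:

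- **That cognition is never tested after baseline.** This is wrong. Outcomes {12} calls 4AT and 3D-CAM cognitive testing, and both continue to day 5. The gap is at 3 months.
- **That the trial cannot answer one of its stated hypotheses.** Neither POCD nor anxiety is among the hypotheses in {7} or the outcomes in {12}, and the Discussion states the objective as delirium, pain and nausea. The abstract's mention of cognitive outcomes names neither POCD nor a 3-month endpoint.
- **That V9 differences will be reported as cognitive benefit.** No planned analysis interprets iADL or SF-36 as cognition. That these scales move with mobility and pain after hip or knee surgery is plausible, but the document has no figure for it.

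The absence of baseline adjustment is also not an error in itself, since a separate analysis plan may cover it.

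**Conclusion.** The point holds as an internal contradiction about V9. The section claims an evaluation of cognitive performance at 3 months, and its own text and Table 1 show that none takes place. POCD and change in cognitive performance cannot be assessed for any patient. The delirium endpoint, the secondary endpoints on pain, medication and PONV, and the sample size are untouched.

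This rests on two readings. First, Table 1 is taken as the complete schedule; the mailed set listed in {18a} agrees with it. Second, the sentence on MoCA, whose punctuation is loose, is taken to mean that MoCA was a baseline entry check and that the 3-month visit had no cognitive tool. Table 1 supports that reading. The anxiety mismatch is real but minor and adds no weight to the main point.

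**What to change.** - In {13}, describe V9 as a functional, quality-of-life and mood follow-up (iADL, SF-36, GDS, BDI). Delete the opening description of it as a survey of cognition, the sentence claiming a valid cognitive evaluation, and the argument from the POCD-testing recommendation. The other stated reason for 3 months, that patients are by then usually home from rehabilitation, suffices for a functional follow-up.
- In the abstract and {13}, state that conclusions on cognition are limited to delirium up to day 5.
- Compare V9 iADL, SF-36 and GDS between arms with adjustment for their V0 values. BDI can only be compared at V9, as it has no baseline.
- In the introduction, remove anxiety from the effects to be tested.

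The cost is a narrower claimed scope and slightly more analysis. No new data, visit or patient burden is needed, because the baseline questionnaires are already in the schedule.
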